## Abstract

**Background:**

Transcutaneous electrical nerve stimulation (TENS) works on the principle of the gate control theory of pain and is used as a nonpharmacological pain management intervention. Music therapy or listening to self-selected music has also been shown to reduce pain intensity, anxiety, and depression. There has been no published literature that has explored whether these modalities can work synergistically.

**Objective:**

This study aims to test the feasibility of a clinical trial comparing TENS alone to TENS combined with self-selected music in participants with persistent low-back pain lasting more than 3 months.

**Methods:**

This will be a prospective, randomized controlled pilot study to compare TENS alone vs TENS combined with participant self-selected music. We hope to enroll 20 participants. The participants will be their own controls, and the order in which the intervention is delivered will be determined by randomization.

**Results:**

The study is open for recruitment from August 2025. The results are expected in 18 months from the start of recruitment. The primary outcome will be the feasibility of the intervention, monitored by adherence rate, dropout rate, and the percentage of the eligible population that consented. Secondary outcomes collected will include pain intensity; mood using the 21-item Depression, Anxiety, and Stress Scale; medication consumption; participant satisfaction; and adverse reactions.

**Conclusions:**

If the pilot trial is feasible and indicates a positive synergistic trend with TENS and music, the trial will help to inform the feasibility for a larger trial with more varied pain diagnoses, including acute and chronic pain.

## Introduction

### Background

Low-back pain is the leading cause of disability across the globe [1]. Pharmacological interventions such as opioids, when used as a long-term management strategy for persistent spinal pain, can result in significant adverse effects [2]. Nonpharmacological noninvasive interventions that facilitate endogenous pain modulatory pathways have the potential to provide improvement in pain and function while minimizing adverse events [3].

Transcutaneous electrical nerve stimulation (TENS) is a nonpharmacological method to manage both acute and persistent pain that works on the principle of gate theory. TENS uses electrical stimulation delivered through surface electrodes encased in a patch to activate large afferent fibers, which causes presynaptic inhibition of afferent nociceptive input at the dorsal horn of the spinal cord [3]. TENS also activates central inhibitory pathways in the brain and spinal cord and acts through multiple neurotransmitters involving opioid, gamma-aminobutyric acid, serotonin, muscarinic, and cannabinoid receptors [4]. Analgesia following TENS can last beyond the period of application for up to 24 hours [5]. There is some evidence that the type of TENS used can impact the duration of analgesia, with higher frequency, lower intensity, or conventional TENS providing faster analgesia but less poststimulation analgesia and low frequency, high intensity, or acupuncture such as TENS providing longer poststimulation analgesia, which can last several hours after the stimulation is terminated [6]. Burst mode TENS, which delivers pulses of electrical stimulation in bursts, is thought to combine the effects of the abovementioned 2 modes and provide quicker onset analgesia that lasts longer than the duration of the stimulation [7]. TENS has been shown to improve functional disability in persistent low-back pain [8].

Music listening interventions, such as music therapy delivered by trained music therapists or listening to self-selected music, have been shown to reduce pain intensity, anxiety, and depression [9]. Functional neuroimaging indicates that this could be due to increasing the descending inhibition as well as changes to the salient stimuli detection circuitry involving somatosensory and prefrontal areas, amygdala, and cingulate cortex, as well as the insula. There is also evidence that reward pathways involving dopamine play a part in the analgesic and mood-altering effects of music listening interventions [10]. Cognitive mechanisms involved in analgesia and mood-altering effects of music listening interventions may include sustained attention on the music rather than pain, associations of self-selected music to pleasant memories, and agency related to selection of the type of music and the volume at which it is played [9]. Listening to self-selected music as well as engaging with the content of the music, or active listening, may reduce pain intensity and improve emotional distress more than music therapy [11]. Listening to self-selected music could have the potential advantage of improved self-efficacy and motivation, increased engagement in daily activities, and incorporation as a cost-effective noninvasive component to the overall pain management strategy [9].

There are no studies in the published literature that combine the abovementioned 2 nonpharmacological interventions in pain management. There is potential for the 2 interventions to act synergistically, providing superior pain relief and improved function compared with either intervention alone, through engagement of central pain modulation pathways and activation of descending inhibitory mechanisms.

### Aims

The primary aim of this study is to test the feasibility of a clinical trial comparing TENS alone to TENS combined with listening to self-selected music in participants with low-back pain with or without leg pain lasting more than 3 months. The results of this feasibility study will be used to inform a larger trial of these interventions in participants with persistent neck and low-back pain lasting more than 3 months. A larger study will be considered feasible if 80% or more of the eligible population consents to the study and 80% or more of the participants are able to adhere to the protocol. The secondary aims are to explore if combining the 2 modalities has a synergistic effect on analgesia and function. A difference of 2 points in the numerical rating scale for pain intensity will be considered significant.

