## Methods

### Overview

TENS with music study will be a prospective, randomized controlled pilot study to compare TENS alone to TENS combined with participant self-selected music. The participants will be randomized to receive 2 weeks of TENS therapy and 2 weeks of TENS with self-selected music using a streaming service, CD player, Long Play, or radio. The order in which this is delivered will be determined by randomization. Therefore, 1 group will receive standard TENS for 2 weeks, followed by TENS with self-selected music for 2 weeks. This order will be reversed in the other group with no washout period. The participants will be compared against themselves for the outcomes, thus reducing the number of participants to power the study. We are hoping to recruit 20 participants for this pilot trial (Figure 1). We will use TENS and TENS with music as part of a holistic pain management plan involving pain neuroscience education, behavior activation, and coping skills training that is individually tailored and not as a stand-alone intervention for pragmatic reasons.

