### Randomization

Participants will be randomized in a 1:1 ratio to 1 of 2 treatment sequences:

Sequence AB: 2 weeks of standard TENS followed by 2 weeks of TENS combined with self-selected musicSequence BA: 2 weeks of TENS combined with self-selected music followed by 2 weeks of standard TENS

Randomization will be performed using a computer-generated allocation list created in Stata (StataCorp LLC) before study commencement. A permuted block design with variable block sizes will be used to ensure balance between sequences throughout recruitment. The randomization seed and code will be archived to allow reproducibility. Allocation concealment will be maintained by storing the randomization list in the Research Electronic Data Capture (REDCap; Vanderbilt University) randomization module, which will reveal the assigned sequence only after a participant has provided informed consent and completed baseline assessments.

The randomization result will be communicated to participants by telephone within 24 hours of their initial assessment. Investigators responsible for outcome collection and statistical analysis will remain blinded to treatment sequence. Participants cannot be blinded due to the pragmatic nature of the intervention.

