### Future Directions

If the trial is feasible and indicates a positive synergistic trend with TENS and self-selected music, it will help to plan for a larger trial with more varied pain diagnoses, including acute and chronic pain other than spinal pain. The aim of a larger study will be to show if combining the 2 modalities of music and TENS will improve pain intensity and function more than TENS alone. The pilot will test the feasibility of using pain diaries as a reliable indicator of gathering information in a larger trial. Future directions could include automated methods for data collection, which could provide more reliable indicators of adherence, function, and medication use.

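### The secondary aim speaks of synergy, but a comparison of TENS with TENS plus music can only estimate what music adds to TENS

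*Protocol article*

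**What the plan says.** The Aims section states: "The secondary aims are to explore if combining the 2 modalities has a synergistic effect on analgesia and function". The Background says what is meant: "There is potential for the 2 interventions to act synergistically, providing superior pain relief and improved function compared with either intervention alone".

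The same idea returns in the forward-looking text. The abstract's Conclusions speak of a pilot that is feasible and "indicates a positive synergistic trend with TENS and music". Future Directions says: "If the trial is feasible and indicates a positive synergistic trend with TENS and self-selected music, it will help to plan for a larger trial".

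The conditions studied are given in the Overview: "The participants will be randomized to receive 2 weeks of TENS therapy and 2 weeks of TENS with self-selected music". Under Randomization: "Participants will be randomized in a 1:1 ratio to 1 of 2 treatment sequences". Both sequences contain the same two conditions in opposite order. The article describes no period or group with music alone, and no randomized period with neither treatment.

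The rest of the plan concerns a single contrast. The second hypothesis, the paired difference in the Power Calculation and the two-level treatment term in the Statistical Methods all compare TENS plus music with TENS. Future Directions sets the larger trial the same comparison.

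The explicit feasibility criterion, also under Aims, is 80% or more consent among eligible patients and 80% or more adherence. It has no pain or synergy term.

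**The concern.** Synergy is a statement about how two treatments act together. In the strict sense, the joint effect exceeds the sum of the separate effects. In the Background's looser sense, the combination is better than each treatment given by itself. Both senses need to know what music does without TENS, and this trial does not observe that.

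The stated aim is therefore one that the data cannot answer. The Background itself reports that listening to music reduces pain intensity. If so, a positive difference is what ordinary additivity would produce, and it carries no evidence specific to synergy.

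The Discussion makes this harder to see. Anticipated Findings calls the expected gain additive and attributes the likely failure to show it to small numbers. The following part of that section promises a picture of the interaction between the modalities. Limitations does not mention the absent conditions. A reader could conclude that a larger trial of the same form would settle the question of synergy. It would not.

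**Working it through.** **Inputs.** Two conditions, TENS and TENS plus music (Overview, Randomization). One contrast, their paired difference (Power Calculation, Statistical Methods). A non-randomized baseline week of pain scores (Outcomes).

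**The plan's own figures first.** Table 2 gives 52, 34, 24, 19 and 15 completed pairs for dz = 0.4, 0.5, 0.6, 0.7 and 0.8, at two-sided α = 0.05 and 80% power. The exact paired t-test calculation (noncentral t, n − 1 degrees of freedom, noncentrality dz·√n) returns the same five numbers. If all 20 participants complete both periods, power at dz = 0.70 is 84.4%, and the smallest dz detectable with 80% power is 0.66. These figures are sound for the contrast they describe.

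**What that contrast estimates.** Write each effect as pain relief relative to neither treatment, on top of the background pain management that all participants receive: T for TENS, M for music, I for the interaction. I > 0 is more than additive, I = 0 additive, I < 0 interference.

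- TENS period: T
- TENS plus music period: T + M + I
- Difference: (T + M + I) − T = M + I

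This is one equation in two unknowns. As an illustration, take an observed gain of 2 points on the pain scale, the size that Aims calls significant. The splits below are examples, not estimates.

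| Music effect M | Interaction I | M + I | Reading |
|---|---|---|---|
| 0 | +2 | 2 | synergy |
| 2 | 0 | 2 | additive |
| 3 | −1 | 2 | interference |

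The data look the same in all three rows.

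**The looser meaning.** Better than either alone requires M + I > 0 (combination against TENS) and T + I > 0 (combination against music). The trial estimates the first. The second is (T + M + I) − M, which needs the music-alone mean.

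**Which conditions would suffice.** Set up the cell means with an intercept, TENS, music and TENS × music. The interaction is estimable only if adding its contrast as an extra row leaves the rank of the design unchanged.

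| Conditions observed | Rank | Rank with interaction row | Interaction estimable? |
|---|---|---|---|
| TENS, TENS + music (as planned) | 2 | 3 | no |
| plus the baseline week as neither | 3 | 4 | no |
| plus music alone, no neither | 3 | 4 | no |
| plus music alone and neither | 4 | 4 | yes |

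Sample size enters none of these rows. Using the baseline week does not help. Adding music alone would allow the looser claim but not the strict one.

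**The case against.** The best defence is that only a label is loose. The hypothesis, the powered contrast, the model and the aim of the larger trial all target the increment over TENS and agree with one another. The aim is secondary, the clinical analyses are called exploratory, and effect sizes with confidence intervals are to be reported for the contrast that the design can estimate. No planned number changes. All of this stands, and it is why the remedy is one of wording.

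It does not remove the point. The term is used for a stated aim and in two statements about what follows the pilot, so it is more than a background slip. Reading it loosely does not help, because the Background's own looser meaning also needs music-alone data. A pilot may be imprecise, but imprecision shrinks with sample size and this gap does not.

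A reader might infer more than the documents support, in three ways.

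- *That the trial has a progression rule that cannot be met.* The only explicit criterion is 80% consent and 80% adherence. The sentences in the abstract's Conclusions and in Future Directions are conditionals that say the pilot will help inform or plan a larger trial, with no threshold, test or decision rule for synergy.
- *That a positive result will be reported as synergy.* The wording invites this, but the article does not commit to it.
- *That adding a music-alone arm would repair the aim.* For the strict meaning it would not, as the third row of the rank table shows.

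**Conclusion.** The point holds as a mismatch between a stated secondary aim and the design. The trial can estimate M + I, the increment from adding self-selected music to TENS. It cannot isolate I, and it cannot show superiority to music alone, at any sample size. There is no numerical size to attach, because the quantity is not identified.

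The conclusion rests on the article describing the conditions completely, which the Overview and Randomization sections appear to do, and on synergy meaning either more than additive or better than each treatment alone. A null or negative difference would count against synergy only under the added assumption that music alone is beneficial, which the trial does not test.

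The primary feasibility outcomes, the 80% criterion, the completed-pairs figures and the planned treatment contrast are untouched. The change is worth making because it brings the claims into line with the analysis and prevents a positive trend from being over-read.

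**What to change.** - In Aims, the abstract's Conclusions and Future Directions, replace the synergistic effect or trend with *incremental benefit of adding self-selected music to TENS*. This matches the hypothesis, the Power Calculation and the Statistical Methods.
- In Anticipated Findings, use the same term in place of additive, and change the later Discussion phrase about the interaction between the modalities accordingly.
- In Limitations, state that synergy cannot be assessed because there is no music-alone condition and no condition without both treatments, and that this is separate from the small sample.
- Do not add a pain-based progression gate. The explicit criterion concerns feasibility and can stay as written.

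The cost is a more modest claim. No condition, visit, sample size or planned model changes. At manuscript submission 4 of the target 20 participants had been enrolled, and the analysis is expected to finish in December 2026, so there should be time to settle the wording before results are read.

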### Hypotheses

First, we hypothesize that administration of TENS combined with music will be equally feasible compared to TENS alone and will be well tolerated by participants. Second, we hypothesize that TENS combined with listening to self-selected music will have improved analgesia compared to using TENS alone.

## Methods

### Overview

TENS with music study will be a prospective, randomized controlled pilot study to compare TENS alone to TENS combined with participant self-selected music. The participants will be randomized to receive 2 weeks of TENS therapy and 2 weeks of TENS with self-selected music using a streaming service, CD player, Long Play, or radio. The order in which this is delivered will be determined by randomization. Therefore, 1 group will receive standard TENS for 2 weeks, followed by TENS with self-selected music for 2 weeks. This order will be reversed in the other group with no washout period. The participants will be compared against themselves for the outcomes, thus reducing the number of participants to power the study. We are hoping to recruit 20 participants for this pilot trial (Figure 1). We will use TENS and TENS with music as part of a holistic pain management plan involving pain neuroscience education, behavior activation, and coping skills training that is individually tailored and not as a stand-alone intervention for pragmatic reasons.

**Figure 1. F1:**
[figure not shown]
CONSORT (Consolidated Standards of Reporting Trials) diagram: TENS with music pilot study. TENS: transcutaneous electrical nerve stimulation.

### Eligibility

All participants aged 18 years or older, presenting with low-back pain lasting more than 3 months with or without referred or radicular limb pain, and attending a pain clinic at a metropolitan tertiary hospital in Australia will be eligible to participate in the study. Participants who have used TENS or music therapy in the past to manage their pain and those participants with a significant hearing impairment, the lack of technical ability to play music through a streaming platform or operate other music listening devices such as an LP or CD player, or an inability to communicate in English will be excluded from participation. Individuals with contraindications to the use of a TENS machine, such as having a permanent cardiac pacemaker, implantable cardioverter defibrillator, or neurostimulators, will also be excluded [12].

### Treatment

TENS will be administered for 1 hour at a time, up to a maximum of 6 times every 24 hours. Participants are free to select from available modes, which include burst, continuous, or modulate. Other parameters, such as pulse width, pulse rate, and pulse intensity, can also be modified by the participant. The pulse intensity of the TENS machine can be adjusted from 0 to 80 mA, and the pulse frequency from 2 to 150 Hz. The aim is to use the frequencies, amplitude, and mode to provide a comfortable paresthesia [13]. The participants can vary the electrode placement to provide the best possible analgesia.

The TENS will be self-administered. Music from a self-selected playlist from a set of genres such as classical, easy listening, pop, rhythm and blues, vocal, and musical will be used. We will use a participant diary to record the duration of TENS each day and the type of music listened to. Music can be listened to with or without headphones. Participants will be provided with a 1-month Spotify (Spotify AB) subscription voucher to enable ad-free music listening.

### Randomization

Participants will be randomized in a 1:1 ratio to 1 of 2 treatment sequences:

Sequence AB: 2 weeks of standard TENS followed by 2 weeks of TENS combined with self-selected musicSequence BA: 2 weeks of TENS combined with self-selected music followed by 2 weeks of standard TENS

Randomization will be performed using a computer-generated allocation list created in Stata (StataCorp LLC) before study commencement. A permuted block design with variable block sizes will be used to ensure balance between sequences throughout recruitment. The randomization seed and code will be archived to allow reproducibility. Allocation concealment will be maintained by storing the randomization list in the Research Electronic Data Capture (REDCap; Vanderbilt University) randomization module, which will reveal the assigned sequence only after a participant has provided informed consent and completed baseline assessments.

The randomization result will be communicated to participants by telephone within 24 hours of their initial assessment. Investigators responsible for outcome collection and statistical analysis will remain blinded to treatment sequence. Participants cannot be blinded due to the pragmatic nature of the intervention.

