### Outcomes

The primary outcome will be the feasibility of the intervention, measured as adherence rate, dropout rate, and the percentage of the eligible population that consented. Adherence rates will include the number of participants using TENS alone or TENS with music regularly more than once per week, adherence to filling out the pain diaries and other patient-reported outcome measures, and attendance at follow-up clinic visits.

Secondary outcomes include the following:

Pain intensity as a numerical rating scale (NRS) score collected before and after each session using a pain diary. The baseline pain will be collected for 1 week before the intervention when they initially attend the clinic.Opioid and other analgesic consumption over a 24-hour period collected in the pain diaryParticipant satisfaction using a 5-point Likert scaleMood measured through the 21-item Depression, Anxiety, and Stress ScaleFunction measured through the Patient-Specific Functional Scale [14]Compliance with other interventions, such as participation in interdisciplinary pain programsAdverse outcomes, including worsening pain and skin reaction to the electrodes used in TENS

All reported adverse reactions will also be collected through the study period when using the TENS machines through entries in the pain diary as well as during interviews with the participants. The self-reported outcome measures, such as the 21-item Depression, Anxiety, and Stress Scale and the Patient-Specific Functional Scale, will be recorded through REDCap forms during the clinic appointments. Figure 2 summarizes the process.

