### Data Collection

A standardized pain diary (Multimedia Appendix 1) will be used for collecting the primary outcome and some of the secondary outcomes, such as medication taken over 24 hours. Specific forms will be used for other secondary outcomes, which are available through REDCap. The data will be stored in a password-protected, secure database via REDCap. The data collected will be deidentified and assigned a study code. The pain management unit will be the custodian of the data stored in the password-protected drive within the local health district computer, with access restricted to the investigators only. The data will be stored for 7 years after the completion of the study. Table 1 summarizes the data collection points.

**Table 1. T1:** Data collection points.

Measure	Frequency	Collection points
Pain diaries	Daily	Baseline, week 1, week 2, week 3, and week 4
Average pain over 24 hours (numerical rating scale)	Weekly	Baseline, week 1, week 2, week 3, and week 4
Medications	Weekly	Baseline, week 1, week 2, week 3, and week 4
Patient-Specific Functional Scale	Fortnightly	Baseline, week 2, and week 4
21-item Depression, Anxiety, and Stress Scale	Fortnightly	Baseline, week 2, and week 4
Pain sites update	1 time	Baseline
Pain duration	1 time	Baseline
Demographics	1 time	Baseline

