### Statistical Methods

This study is a 2-period, 2-sequence crossover pilot trial without a washout period between treatments. Analyses will primarily focus on feasibility outcomes (recruitment, adherence, data completeness, and dropout) using descriptive statistics (means, medians, and proportions) with 95% CIs rather than formal hypothesis testing. These feasibility metrics will inform the practicality of conducting a larger definitive trial.

For the primary clinical outcome of pain intensity, exploratory analyses will first be conducted using paired *t* tests to compare mean scores between TENS and TENS with self-selected music within participants. Normality of paired differences will be assessed using graphical methods and the Shapiro-Wilk test. If assumptions are violated, the Wilcoxon signed-rank test will be applied as a nonparametric alternative. Categorical variables (eg, adverse events and compliance categories) will be analyzed initially using chi-square tests, or Fisher exact test if expected cell counts are small. All tests will be 2-sided with a significance level of *α*=.05.

Following these preliminary analyses, formal modeling tailored to the crossover design will be undertaken. Linear mixed-effects models will be specified with fixed effects for treatment (TENS vs TENS with self-selected music), period, and sequence, and a random intercept for participant to account for within-participant correlations. Because no washout period is present, carryover effects will be explicitly assessed by including a prior-treatment term and by examining period×sequence interactions. If evidence of carryover is observed, analyses will be restricted to first-period data as a sensitivity check, treating it as a parallel-group comparison.

Secondary outcomes (mood, function, satisfaction, medication use, and adverse events) will be analyzed using appropriate mixed-effects regression models: linear for continuous outcomes, cumulative logit for ordinal outcomes, negative binomial for counts, and logistic for binary outcomes. These analyses are exploratory in nature. Given the pilot design and small sample size, no formal correction for multiple testing will be applied; instead, effect sizes and CIs will be reported to guide future sample size calculations.

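### The sequence is telephoned within 24 hours of the first assessment, but baseline pain is a one-week diary tied to that visit, so on the plain reading most baseline ratings follow disclosure

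*Protocol article*

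**What the plan says.** Four places in the protocol article bear on the order of baseline and allocation.

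- **Randomization, reveal rule.** The list is held in the REDCap randomization module, "which will reveal the assigned sequence only after a participant has provided informed consent and completed baseline assessments".
- **Randomization, next paragraph.** "The randomization result will be communicated to participants by telephone within 24 hours of their initial assessment". The paragraph adds: "Participants cannot be blinded due to the pragmatic nature of the intervention".
- **Outcomes, pain intensity.** "The baseline pain will be collected for 1 week before the intervention when they initially attend the clinic". Analgesic consumption is recorded in the same diary.
- **Data Collection, Table 1.** Pain diaries are daily, with collection points "Baseline, week 1, week 2, week 3, and week 4". The weekly 24-hour average pain score and medications have the same collection points.

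For the analysis of pain, Statistical Methods plans paired tests between the two treatments and then a crossover model: "Linear mixed-effects models will be specified with fixed effects for treatment (TENS vs TENS with self-selected music), period, and sequence". No baseline covariate is named.

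**The concern.** A week of daily entries that begins at the first attendance cannot be complete 24 hours after that attendance. Either the telephone call breaks the reveal rule, or the phrase about baseline assessments silently leaves out baseline pain. The text says neither.

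Two things are at stake.

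1. **Baseline values.** Participants rate their own pain and know their sequence once called. Ratings given while knowing whether music comes first or second are open to expectation. The authors take such effects seriously: the Discussion explains that previous users of TENS or music were excluded because of possible placebo effects. Diary entries on medication in that week are exposed in the same way. This bears on the comparability of the two sequences at baseline, on any change-from-baseline summary, and on the first-period check if that check uses baseline.
2. **Feasibility figures.** Dropout and adherence are part of the primary outcome. Under the 24-hour call, someone who gives up during the baseline week has already been randomized. Under the reveal rule, the same person never is. The two rules give different denominators for the primary result.

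**Working it through.** The protocol states no figure on this point, so there is none to reproduce. The check is a timeline and a count.

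**Inputs**
- Disclosure: at most 24 hours after the initial assessment (Randomization).
- Length of baseline pain collection: 1 week = 7 × 24 = 168 hours (Outcomes).
- Start of the baseline week: the first clinic attendance. This is the natural reading of Outcomes, not an explicit statement.
- Target N = 20 (Overview); adherence criterion 80% (Aims).

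**Step 1: share of the baseline week after disclosure.** With disclosure at h hours, share = 1 − h/168.

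| Disclosure at | Hours left | Share after disclosure |
|---|---|---|
| 0 h | 168 | 100% |
| 12 h | 156 | 92.9% |
| 24 h | 144 | 85.7% (6 of 7 days) |

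Even at the latest permitted time, 6 of the 7 diary days follow disclosure. If the call waits until the week has ended, the share is 0%.

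**Step 2: can any reading reconcile the statements?**

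| Reading | Reveal rule | 24-hour call | One-week daily baseline diary |
|---|---|---|---|
| Baseline assessments include the diary, which starts at the visit | kept | cannot be met (earliest reveal is day 7) | kept |
| Baseline assessments mean only what is done at the visit | kept by excluding baseline pain, which is not stated | kept | kept, but 86–100% falls after disclosure |
| The past week's pain is recalled at the visit | kept | kept | fits poorly with a daily diary; Limitations treats late completion as a source of recall bias |
| The initial assessment is a visit that closes the diary week | kept | kept | fits poorly with Outcomes, which ties the week to first attendance |

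The last two readings remove the conflict, but neither is stated and each sits badly with another sentence.

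**Step 3: effect on the feasibility count.** One participant who is randomized and then stops during the baseline week adds 1/20 = 5 percentage points to dropout. As an illustration, assume 10% stop in that week: 0.10 × 20 = 2 people.
- All 20 in the denominator: the 80% adherence criterion needs 0.80 × 20 = 16 adherent participants.
- Only the 18 who complete the week: 0.80 × 18 = 14.4, so 15.

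With exactly 15 adherent participants the trial fails under the first count (15/20 = 75%) and passes under the second (15/18 = 83.3%). The 10% is an assumption; the protocol gives no rate for this week. With one such loss the required count stays at 16, since 0.80 × 19 = 15.2 rounds up to 16.

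**Step 4: does baseline enter the planned pain analysis?** The paired test compares the two treatment periods within each person. The mixed model names treatment, period and sequence. A shift in baseline ratings enters neither as specified.

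**The case against.** The strongest objection is that the order is inferred. Outcomes gives no day numbers, the initial assessment is not defined, Table 1 does not date its baseline column, and neither the workflow figure nor the diary appendix is available here. Any of these could show a compatible order. This stands as a limit: the 6-of-7-days figure holds only if the diary starts at the first visit. It does not make the printed sentences consistent.

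A second objection is that the consequence is small, and most of it stands. Pain is a secondary, exploratory outcome, participants are unblinded throughout, and the main contrast does not use baseline.

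A third is that randomizing only people who finish the diary would work as a run-in. It would remove poor adherers and improve the adherence and dropout figures, although diary completion is itself a feasibility outcome. This also stands, and the fix has to deal with it.

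Some stronger readings are tempting but unsupported:

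- **Allocation concealment is broken.** It is not: the sequence stays hidden until after consent, so enrolment cannot be steered by it. What is breached is the protocol's own baseline-before-reveal rule.
- **The treatment effect on pain is biased.** The within-participant contrast does not involve baseline. The first-period comparison is a sensitivity check used only if carryover appears, and no change-from-baseline endpoint is named for it. The documents also give nothing from which to size an expectation effect in NRS points.
- **The sequences become unbalanced.** Nothing shows that losses in the baseline week would differ by sequence.

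**Conclusion.** The point holds as a contradiction in timing with a modest consequence. On the plain reading, the reveal rule, the 24-hour call and the one-week baseline diary cannot all be met, and 86–100% of baseline pain and medication diary entries would be made when the participant may already know the sequence.

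The exposure is limited to the baseline values and whatever uses them, and to how people who stop in the baseline week are counted, at 5 percentage points each with 20 participants. The main pain comparison and concealment at enrolment are untouched.

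The conclusion rests on two assumptions: the baseline week starts at the first attendance, and the unavailable workflow figure does not set a different order. It is worth correcting because the correction is cheap, because it agrees with the rule the protocol already states, and because the pilot's procedures are meant to inform a larger trial.

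**What to change.** 1. State the day on which the baseline week starts and the day on which it ends, and say which assessments must be finished before the sequence is revealed.
2. Release the REDCap allocation and telephone the participant only once the baseline week has ended. In the Randomization section, time the 24-hour limit from the end of the one-week baseline diary instead of from the initial assessment.
3. In the feasibility results, report separately the consented participants who do not complete the baseline week, so that the later reveal does not become a hidden run-in that flatters adherence and dropout.
4. Flag participants enrolled under the present timing. The Results section reports 4 of the planned 20 at submission, which left 20 − 4 = 16 who could follow the corrected order.

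**Cost.** Allocation comes one week later. Someone must confirm diary completion at the call, and this relies on the participant's own report, since Limitations notes that there is no concurrent electronic monitoring. No extra visit is needed, because allocation is already given by telephone, and the target sample size and power calculation do not change.
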